### Randomization

Following informed consent, participants will be randomized in a 1:1 allocation to a sequence of either immersion relaxation using VR in the first period, followed by no immersion VR in the second treatment period, or no immersion VR in the first period, followed by immersion relaxation using VR in the second period, based on a computer-generated random number that is concealed via a sealed envelope. One of the researchers conducts this step. The allocation will not be disclosed to the other researchers who conduct the trial until the participant is enrolled and assigned. In addition, researchers who perform the statistical analyses will be blinded to the group allocation.

### Intervention group: virtual reality immersive relaxation

Participants in the VR immersion group (intervention group) will be asked to wear the VR headset (Pico G2 4K; Pico Technology Co., Ltd.; China) and choose the 360-degree panoramic videos on natural scenery around the world at https://vr.iqiyi.com/ based on their preferences to relax themselves in the resting room. In order to avoid selection bias stemming from the content of the videos, such as terrifying videos or rock songs, which may influence relaxation, the content of videos is limited to natural scenery. Considering the limitation of resting time in clinical practices, participants experience VR immersion for only 20 min for each time and they will be asked to watch videos for 20 min at 23:30 and at 07:30 of the next day. The timepoints are chosen based on our preliminary data that most first-line anesthesiologists would feel stress and overworked after 23:00, and the handover time of the night shifts (08:00 of the next day). In addition, according to our preliminary study, it took about 5 min to complete all the assessments at each timepoint. Thus, the participants are asked to complete the NASA-TLX, CPSS, VAS, and MFI-20 5 min before the specified timepoint. When the participants are watching the videos, anesthesiologists with the same qualifications will take over their work until the VR immersion is complete.

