**Discussion:**

It is unknown whether the use of VR technology during the night shift can reduce stress among anesthesiologists. With the widespread use of VR technology, a positive result in this trial could spur hospitals to apply VR technology to reduce stress among night-shift doctors in every department and provide a relatively relaxed working environment.

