**Fig. 1 Fig1:**
[figure not shown]
The crossover design of the study

The primary outcome of the study will be the NASA Task Load Index (NASA-TLX) at 07:50 of the next day, which consists of six dimensions rated on a 100-point scale in each dimension (physical demand, mental demand, temporal demand, effort, performance, and frustration) and is widely used to measure the mental workload [22, 23]. Secondary outcomes will be the Chinese Perceived Stress Scale (CPSS), perceived stress scores (visual analogue scale (VAS)), and Multidimensional Fatigue Inventory (MFI-20) scores; the level of satisfaction among participants; heart rate (HR); blood pressure (BP); and incidence of arrhythmia, chest tightness, headache, and palpitations at all the recorded timepoints. The CPSS was used to assess the severity of participants’ psychological stress as earlier reported [24]. Perceived stress score was assessed via the VAS score, which was defined as the length in millimeters from 0 (no stress) to 10 (unbearable stress) [25]. The MFI-20 score was used to quantify the impact of fatigue [26], including five independent subscales of fatigue: general fatigue, mental fatigue, physical fatigue, reduced activity, and reduced motivation.

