### Control group: the routine night-shift group

Participants in the control group will undergo a routine night shift without the VR immersion experience.

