## Discussion

This study will be the first to evaluate the potential effectiveness of VR technology in reducing stress among night-shift anesthesiologists. Work overload, long working hours, and continuous noise pollution [30, 31] are among the factors that cause physical and mental problems among anesthesiologists, such as psychological distress, burnout syndrome (BOS), and memory and attention problems [32, 33]. It has been reported that mental fatigue is the main cause of medical error among anesthesiologists [34] as well as the main reason for the high proportion of suicides among these doctors [35]. A study showed that the risk of medical accidents increases exponentially with each hour of work after the doctor has worked for 9 h consecutively. Moreover, the impairment of psychomotor function may be equivalent to a blood alcohol concentration of 0.1% if the doctor has experienced 24 h of sustained wakefulness; this concentration is higher than the legal limit for driving in most states in the USA [36]. It has also been reported that the rate of burnout among anesthesiologists is 48%, higher than that among all physicians among the specialties studied [37]. The burnout rate among Chinese anesthesiologists is 69%, while their consultation rates are 73% [38]. It is an urgent necessity to take more measures to curb psychological distress without increasing the number of anesthesiologists.

VR technology has been widely used in clinical practice to treat mental illnesses and reduce preoperative anxiety in both healthcare providers and patients [16, 17, 19]. Shah et al. [39] found that stress was the primary target and depression was the secondary target in the VR mood induction procedure study. The current study would provide evidence affirming the use of VR technology to reduce stress among night-shift anesthesiologists. These results might be attributed to the fact that watching VR videos could reduce the long hours of night-shift work, distract the anesthesiologists, and allow them to rest, thus making them positive and vibrant again.

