However, there are still several limitations in the study. First, because of the connectivity issues of VR technology, a nonimmersive environment may arise, which may interfere with participant relaxation and the subsequent level of satisfaction. Second, in the current study, to better ensure the safety of patients, we will arrange another extra qualified anesthesiologist to take over the participants’ work during the VR immersion. However, this might be unlikely in the real-world where extra anesthesiologists are not always present. We hope the results of the study may spur managers to take measures to enable the anesthesiologists to enjoy VR entertainment during the night shift in the future. Third, the study is a single-center, crossover design with a small sample size. Therefore, it is better to confirm the preliminary results by conducting a large-scale multicenter study.

Although VR technology has been widely used in biomedical fields, it is still unknown whether the use of VR can reduce stress among night-shift anesthesiologists during working hours. A positive result in this trial could spur hospitals to apply the technology to reduce stress among night-shift doctors in every department, thus creating a relatively relaxed working environment that can benefit both doctors and patients.

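### Relief from work comes only with the VR sessions, so the trial can estimate the effect of VR plus two covered 20-minute breaks, not the effect of VR technology

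*Protocol article*

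**What the plan says.** **VR nights.** The intervention section has participants watch VR in the resting room for 20 minutes at 23:30 and at 07:30. It adds: "When the participants are watching the videos, anesthesiologists with the same qualifications will take over their work until the VR immersion is complete". The limitations paragraph of the Discussion confirms that this is additional staffing tied to the sessions: "we will arrange another extra qualified anesthesiologist to take over the participants’ work during the VR immersion".

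**Control nights.** The whole description is one sentence: "Participants in the control group will undergo a routine night shift without the VR immersion experience". No cover or matched break is mentioned there or under Study design.

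**Primary outcome.** Study design sets it as the NASA-TLX at 07:50 and says of the scale that it "is widely used to measure the mental workload". Data collection places 07:50 (T6) at the end of the second session. Perceived stress is measured separately by the CPSS and a VAS, both secondary outcomes.

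**Planned conclusion.** The Abstract says that "a positive result in this trial could spur hospitals to apply VR technology to reduce stress among night-shift doctors". The Discussion expects the study to support VR technology as a way to reduce stress. It explains the expected result by saying that "watching VR videos could reduce the long hours of night-shift work, distract the anesthesiologists, and allow them to rest".

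**The concern.** VR nights and control nights differ in two ways: the headset, and time off work with someone else covering. The two occur together on every VR night, and neither is described for any control night. Randomizing the sequence and using each participant as their own control removes differences between people. It does not separate two components that are always given together.

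The timing adds to the problem. A workload scale is completed as a period of relief ends in one condition, with no equivalent relief described in the other. Two of the three mechanisms that the Discussion offers, less working time and rest, need no headset.

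At stake is what a positive result may be used for. Hospitals would read it as a reason to adopt VR, although arranging cover for a break might give some or all of the benefit. A lower workload score would also be reported as lower stress, which is a different construct with its own scales in this trial.

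**Working it through.** **1. The two conditions side by side**

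| | VR night | Control night |
|---|---|---|
| VR at 23:30 and 07:30 | yes, 20 min each | no |
| Extra colleague covering the work | yes, during both sessions | none described |
| NASA-TLX at 07:50 | as the second covered session ends | no covered session described |

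Covered time is 2 × 20 = 40 min. The shift runs from 17:30 to 08:00, which is 14.5 h or 870 min, so the cover takes 40/870 = 4.6% of it. The share is small, but its second half ends at the primary assessment. The intervention section also has the scales filled in during the 5 minutes before each timepoint. For 07:50 that means from about 07:45, still within the session, so the score falls at the end of the break or directly after it.

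**2. The planned sample size**

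Inputs from Sample size estimation: difference 65.5 − 55.7 = 9.8 points; SD of the difference 12.1; two-sided α 0.05; power 80%; N = 26.

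Test: 2 × 2 crossover t-test with df = N − 2, standard error SD_diff/√N, and noncentrality δ/(SD_diff/√N).

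- 12.1 taken as the within-subject SD: SD_diff = 12.1 × √2 = 17.1. At N = 26 the standard error is 17.1/√26 = 3.36, the noncentrality 9.8/3.36 = 2.92, and the power 0.800. This reproduces the plan's 26.
- 12.1 taken as labelled, the SD of the difference: the standard error is 12.1/√26 = 2.37, the noncentrality 4.13, and the power 0.977. N = 16 would be enough.

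The text does not settle which SD applies to the final comparison, so both are carried forward.

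**3. Chance of a significant result if VR adds nothing**

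The break-only effects are assumptions. The 4.9 points is half of 9.8; 3 points is a smaller illustrative value. N = 26, critical t = 2.064 on 24 df.

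| Assumed break effect | Noncentrality (SD_diff 17.1) | P(significant) | Noncentrality (SD_diff 12.1) | P(significant) |
|---|---|---|---|---|
| 3.0 | 3.0/3.36 = 0.89 | 0.14 | 3.0/2.37 = 1.26 | 0.23 |
| 4.9 | 4.9/3.36 = 1.46 | 0.29 | 4.9/2.37 = 2.06 | 0.51 |

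With no break effect and no VR effect the figure would be 0.05.

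**4. The planning effect**

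The 9.8 points is a before/after change in 14 subjects. If the pilot sessions also took participants off duty, which the text does not say, this figure already contains some effect of the break.

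**The case against.** The comparison of VR with a routine night shift is stated openly and is a legitimate one: a department deciding whether to introduce covered VR sessions wants exactly that contrast. The authors name rest as a mechanism, list the extra cover among the limitations, speak of potential effectiveness, and call the results preliminary. That stands as a defence of the design. It does not rescue the attribution. The limitation concerns only whether cover would be available in ordinary practice, not whether the cover explains the result, and the Discussion still credits VR technology.

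Three stronger readings are tempting, and the documents do not support them.

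- **That a covered break would account for the whole effect.** No break-only effect is given, so its share is unknown.
- **That control participants work without pause.** The text says only that the shift is routine, and the intervention section refers to limited resting time in practice, so informal rest may occur. What is missing is a described equivalent of the cover.
- **That the 07:30 score before the second session gives a clean comparison.** It avoids scoring straight after relief, but it still follows the 23:30 covered break. Data collection also states the six timepoints only for the intervention group; the figures, which are not shown, may say more.

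**Conclusion.** The point holds as a limit on interpretation. The trial can validly estimate the effect of VR plus two covered 20-minute breaks against a routine night shift. It cannot say how much of that effect is due to VR. It would be wrong to infer that the trial is uninterpretable or that VR does nothing.

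This conclusion needs no numerical assumption: it follows from cover being described for the VR sessions only. The size does rest on assumptions. With no VR effect and a break worth 3 to 4.9 points, a significant result at N = 26 has probability 14% to 29% with an SD of the difference of 17.1, the reading that reproduces the planned N, or 23% to 51% with 12.1 as labelled. A different break effect would move these figures in either direction.

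**What to change.** 1. Restate the objective and conclusion as the effect of VR immersion with two covered 20-minute breaks compared with a routine night shift.
2. Remove or soften the attribution to VR technology in the Abstract and in the Discussion, including its closing paragraph.
3. In the limitations paragraph, name the cover given only with VR as a confound for the cause of any difference, as well as a feasibility limit.
4. Base any claim about stress on the CPSS and VAS, which are already planned, and not on the NASA-TLX alone.

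These are changes of wording and need no new data. The cost is a narrower claim. A matched covered break on control nights would address attribution directly, but it is not asked for here: it needs extra staff, and the trial is already under way, so a change of control condition would mix two comparators. It is better kept for a later study.

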### Control group: the routine night-shift group

Participants in the control group will undergo a routine night shift without the VR immersion experience.

### Data collection

The participants’ general characteristics, including sex, age, body mass index (BMI), heart rate (HR), blood pressure (BP), and electrocardiogram (ECG) data, will be collected. To assess the effect of VR immersion on stress among night-shift anesthesiologists, data will be collected from participants in the intervention group at six timepoints: baseline status (07:50 am, T1), initiation of night shift (17:30, T2), before first VR immersion (23:30, T3), after first VR immersion (23:50, T4) on the day that they work the night shift and before second VR immersion (07:30, T5), and after first VR immersion (07:50, T6) of the next day. At each timepoint, participants will be asked to measure their stress status via completing the scales which included NASA-TLX, CPSS, VAS, and MFI-20. In addition, ECG will be measured using a mobile ECG recorder (CardioLearn; HeartVoice Medical Technology Co., Ltd., Anhui, China) at each timepoint following the manufacturer’s instructions. The mobile device has been widely used in China to simply measure the ECGs and automatically analyze their results based on a novel deep learning-based cloud service as earlier reported [27, 28]. Furthermore, the anesthesiologists will be invited to record their ECG whenever they feel discomfort during the night shift. The incidence of arrhythmia, level of satisfaction, and incidence of chest distress, headache, or heart palpitations will also be recorded by the researchers. The data recording flow chart is presented in Fig. 2 and the SPIRIT figure is shown in Fig. 3.

**Fig. 2 Fig2:**
[figure not shown]
The data recording flow chart of the study

**Fig. 3 Fig3:**
[figure not shown]
SPIRIT figure of the study

Two researchers blinded to the grouping are responsible for data entry and reconciliation. Both the paper and electronic data are retained by the corresponding authors, and the data will be kept forever after the trial is completed.

### Reporting of compliance and adverse events

To avoid possible bias, participants who had experienced something very pleasant or sad during the washout time will be asked to report their own emotion status before the second enrollment. This would be recorded and judged by two independent psychologists and those who get married or promoted, whose child is born, or whose family member is dead would be excluded from the final analysis. It has been reported that young people are more vulnerable to physical discomfort, such as seizures, severe dizziness, eye twitching, or blackouts triggered by light flashes when wearing a VR headset [29]; therefore, for participants who experience any discomfort during the VR immersion procedure, the trial can be stopped, and the participants will be treated accordingly. All these events are recorded and reported. To ensure the safety of patients, anesthesiologists with the same qualifications will take over the participants’ work during the VR immersion.

### Statistical analysis

#### Sample size estimation

The sample size for this study was estimated using the PASS program 15.0.5. Based on our preliminary data from 14 subjects, the mean ± SD of the NASA-TLX was 65.5 ± 16.8 before the intervention and 55.7 ± 18.2 after the intervention, and the SD of the difference was 12.1. According to tests for the difference between two means in a 2 × 2 crossover design, assuming a two-sided *α* of 0.05 and a statistical power of 80%, 26 participants are needed. To account for a potential dropout rate of 10%, we aim to recruit a sample size of 30 participants in total, and thus, 15 participants are needed for each sequence.

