**Methods:**

In this randomized controlled, crossover, single-center clinical trial, a total of 30 anesthesiologists will be enrolled and randomized in a 1:1 allocation to either the VR immersion group (intervention group) or the routine night-shift group (control group) with a washout of 1 week. Anesthesiologists in the intervention group will undergo VR immersion twice, while anesthesiologists in the control group will not watch VR videos during the night shift. The primary outcome will be the difference in the NASA Task Load Index (NASA-TLX) score between the two groups. Secondary outcomes will include the Chinese Perceived Stress Scale (CPSS), perceived stress scores (visual analogue scale (VAS)), and Multidimensional Fatigue Inventory (MFI-20) scores; levels of satisfaction among the participants; incidence of arrhythmia; and incidence of chest tightness, headache, and palpitations.

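### The stated difference, SD, power and sample size do not agree with one another, and the difference and SD come from a before–after pilot change, not from VR versus control

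*Protocol article*

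**What the plan says.** Under Sample size estimation, the protocol article draws on 14 pilot subjects. It gives the NASA-TLX as "65.5 ± 16.8 before the intervention and 55.7 ± 18.2 after the intervention", adds "and the SD of the difference was 12.1", and names a test of two means in a 2 × 2 crossover. The error rates are two-sided 0.05 and 80% power, and the result is "statistical power of 80%, 26 participants are needed". A 10% dropout allowance raises this to 30, or 15 per sequence.

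The Abstract defines the comparison to be tested: "The primary outcome will be the difference in the NASA Task Load Index (NASA-TLX) score between the two groups". Study design places the primary NASA-TLX reading at 07:50 on the morning after the shift. Setting says each anesthesiologist works one night shift per arm, and the washout between periods is one week.

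**The concern.** There are two separate problems.

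- **Internal consistency.** The paragraph gives every input to a standard calculation, so the result can be checked. With 12.1 used as labelled, 26 is far more than 80% power requires. Either the label, the value entered or the stated power is wrong, and the reader cannot tell which.
- **Relevance of the inputs.** The 9.8-point difference and its SD are changes from before to after VR. The trial tests a difference between a VR night and a control night. A before–after change includes whatever would have happened without VR. Its SD reflects the correlation between two readings around the intervention, not between two nights at least a week apart.

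At stake is whether the claimed 80% describes this trial. If it does not, a null result is hard to interpret, because the difference the trial could reliably have detected is not established.

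**Working it through.** **Inputs (Sample size estimation).** Difference δ = 65.5 − 55.7 = 9.8; SD 12.1; two-sided α = 0.05; power 80%; stated N = 26, raised to 30.

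**Formula.** For a 2 × 2 crossover with equal sequences, SE = SD_diff/√N and df = N − 2. Power comes from the noncentral t distribution with noncentrality δ/SE. If the within-subject SD is S_w, then SD_diff = √2 × S_w.

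**1. Trying to reproduce 26 with 12.1 as labelled (SD_diff = 12.1)**

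| N | Noncentrality 9.8√N/12.1 | Power |
|---|---|---|
| 14 | 3.03 | 79.4% |
| 15 | 3.14 | 82.6% |
| 16 | 3.24 | 85.3% |
| 26 | 4.13 | 97.7% |
| 30 | 4.44 | 99.0% |

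The required N is 15, or 16 for equal sequences. Other settings with the same SD also miss 26: one-sided 80% gives 12, two-sided 90% gives 19 (20 for equal sequences), and two-sided 95% gives 22.

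**2. Readings that do return 26**

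- 12.1 as within-subject SD: SD_diff = 12.1 × √2 = 17.1. Power is 76.5% at N = 24 and 80.0% at N = 26.
- 16.8 (the pilot SD before VR) as SD_diff: power is 78.0% at N = 24 and 81.4% at N = 26.

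The first matches the stated 80% more closely, but both return 26.

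**3. Is 12.1 plausible under either label?**

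- As a paired-difference SD, it implies a correlation of (16.8² + 18.2² − 12.1²)/(2 × 16.8 × 18.2) = 0.76.
- As a within-subject SD, with a single-reading SD of √[(16.8² + 18.2²)/2] = 17.5, it implies 1 − 12.1²/17.5² = 0.52.

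Both are possible, so the pilot figures do not settle which label is right.

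**4. Dropout.** 26/0.9 = 28.9, so 29, and 30 for equal sequences. This step is sound.

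**5. Power for the contrast actually tested.** The document gives no VR-versus-control difference and no between-night SD, so these are assumptions. With a per-night SD of 17.5 and between-night correlation ρ, SD_diff = 17.5 × √[2(1 − ρ)]. Holding the effect at 9.8:

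| ρ | SD_diff | Power, N = 26 | Power, N = 30 |
|---|---|---|---|
| 0.3 | 20.7 | 64% | 71% |
| 0.5 | 17.5 | 78% | 84% |
| 0.6 | 15.7 | 86% | 91% |
| 0.76 | 12.1 | 98% | 99% |

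With an assumed effect of 5 points instead, power at N = 26 is 52% for SD_diff = 12.1 and 30% for SD_diff = 17.1. At N = 30 the figures are 59% and 34%.

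**The case against.** The best defence is that the SD discrepancy harms nothing by itself. If 12.1 was entered as the within-subject SD, then 26 and 80% are right and only the label is wrong. If the label is right, 26 exceeds the 15 or 16 needed. On neither reading is the trial short of participants for its own 9.8 points. This stands, and it is why the matter is a reporting correction and not a call for more participants.

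A reader might infer that the SD mix-up is established. It is not: the software input is not shown, and 16.8 used as the SD of the difference also gives 26.

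A reader might also infer that the pilot had no control condition, or that the between-night correlation was never estimated. A condensed article cannot show either. It describes no control condition and reports no such correlation, and that is as far as the text goes.

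Finally, the assumed ranges in the working borrow their per-night SD from the same pilot, and 0.76 is simply the pilot's before–after correlation. This also stands. The ranges show how sensitive power is to these inputs; they do not estimate it.

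The defence does not reach the second problem. The calculation is stated in full, so its basis is not a detail left to another document, and that basis is a different contrast from the primary one.

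**Conclusion.** The point holds at moderate severity.

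- **Inconsistency.** This is arithmetic and rests only on the paragraph's own figures: the stated inputs call for 15 or 16 participants, not 26. Confusion between the within-subject SD and the SD of the difference is the likely cause, but not a proven one.
- **Contrast.** The 80% is unsupported for VR versus control at 07:50, because neither the difference nor the SD is reported for that comparison.

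The two problems can pull in opposite directions. Taken at face value, the SD label makes the trial generously sized; a lower between-night correlation or a smaller VR–control difference would make it underpowered. The documents do not support saying that the trial is in fact underpowered, or that 98% should replace 80% as its power for the primary comparison.

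**What to change.** Keep N = 30 and rewrite the sample size paragraph:

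1. State which SD was entered. If it was the within-subject SD, relabel it as within-subject SD 12.1, SD of the difference 17.1; N = 26 and 80% then stand. If it was not, correct the stated SD or power so that the figures agree.
2. Say that 9.8 is a before–after pilot change that is assumed to apply to VR versus control at 07:50, and give any justification available.
3. Report power as a range over both the between-night correlation and the effect, at 26 and at 30, with the assumed per-night SD shown. The figures in the working can serve as a starting point, or be replaced by any between-night data the sponsor holds.

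The cost is one paragraph. Enrolment, allocation and the dropout allowance do not change.
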